# Evaluating remote facilitation intensity for multi-national translation of nurse-initiated stroke protocols (QASC Australasia): a protocol for a cluster randomised controlled trial

**DOI:** 10.1186/s13012-023-01260-9

**Published:** 2023-01-26

**Keywords:** Stroke, Facilitation, Implementation, Remote, Process evaluation, Care bundle, Economic evaluation

## Abstract

**Background:**

Facilitated implementation of nurse-initiated protocols to manage fever, hyperglycaemia (sugar) and swallowing difficulties (FeSS Protocols) in 19 Australian stroke units resulted in reduced death and dependency for stroke patients. However, a significant gap remains in translating this evidence-based care bundle protocol into standard practice in Australia and New Zealand. Facilitation is a key component for increasing implementation. However, its contribution to evidence translation initiatives requires further investigation. We aim to evaluate two levels of intensity of external remote facilitation as part of a multifaceted intervention to improve FeSS Protocol uptake and quality of care for patients with stroke in Australian and New Zealand acute care hospitals.

**Methods:**

A three-arm cluster randomised controlled trial with a process evaluation and economic evaluation. Australian and New Zealand hospitals with a stroke unit or service will be recruited and randomised in blocks of five to one of the three study arms—high- or low-intensity external remote facilitation or a no facilitation control group—in a 2:2:1 ratio. The multicomponent implementation strategy will incorporate implementation science frameworks (Theoretical Domains Framework, Capability, Opportunity, Motivation – Behaviour Model and the Consolidated Framework for Implementation Research) and include an online education package, audit and feedback reports, local clinical champions, barrier and enabler assessments, action plans, reminders and external remote facilitation. The primary outcome is implementation effectiveness using a composite measure comprising six monitoring and treatment elements of the FeSS Protocols. Secondary outcome measures are as follows: composite outcome of adherence to each of the combined monitoring and treatment elements for (i) fever (*n*=5); (ii) hyperglycaemia (*n*=6); and (iii) swallowing protocols (*n*=7); adherence to the individual elements that make up each of these protocols; comparison for composite outcomes between (i) metropolitan and rural/remote hospitals; and (ii) stroke units and stroke services. A process evaluation will examine contextual factors influencing intervention uptake. An economic evaluation will describe cost differences relative to each intervention and study outcomes.

**Discussion:**

We will generate new evidence on the most effective facilitation intensity to support implementation of nurse-initiated stroke protocols nationwide, reducing geographical barriers for those in rural and remote areas.

**Trial registration:**

ACTRN12622000028707. Registered 14 January, 2022.

**Supplementary Information:**

The online version contains supplementary material available at 10.1186/s13012-023-01260-9.

Contributions to the literature
This study will test whether high- or low-intensity external remote facilitation versus no external facilitation is more effective at improving implementation of the Fever Sugar Swallow (FeSS) Protocols for stroke patients in Australia and New Zealand.This study leverages a cluster randomized trial design, implementation science frameworks, a process evaluation and economic evaluation to enhance understanding of facilitation, and its contribution to implementation of evidence-based stroke interventions.This study aims to provide evidence on the most effective facilitation intensity for large-scale implementation of the FeSS Protocols in stroke patients.Findings will be relevant to FeSS Protocol adoption worldwide.

## Background

Facilitated implementation of a nurse-led intervention to manage *Fe*ver, hyperglycaemia (‘*S*ugar’) and *S*wallowing (FeSS Protocols) in 19 stroke units in New South Wales (NSW), Australia resulted in a 16% reduction in death and disability for patients with stroke in the Quality in Acute Stroke Care (QASC) Trial [1], with a sustained 20% improvement in survival 4 years post-stroke [2]. Subsequent scale-up of the Protocols to all 36 NSW stroke services in 2014 demonstrated improvements in Protocol adherence in the Quality in Acute Stroke Care Implementation Project (QASCIP) [3]. No further systematic implementation of the FeSS Protocols was initiated across Australia. To date, systematic implementation of the FeSS Protocols has not occurred in New Zealand.

In 2017, a ‘strong recommendation’ for use of standardised protocols to manage fever, glucose and swallowing difficulties in patients following acute stroke was included in the Australian and New Zealand Clinical Guidelines for Stroke Management [4]. However, the most recent 2021 Australian national acute services stroke audit showed that fever, hyperglycaemia and swallow management remained sub-optimal with only half (50%) of patients with fever ≥37.5°C receiving paracetamol within an hour, only 29% receiving insulin within 1 h of the first elevated finger prick glucose ≥10mmol/L and only 60% of patients receiving a swallow screen/assessment prior to oral medications, food, or drink [5]. In New Zealand, the most recent nationwide stroke audit in 2018 was conducted as part of the Reducing Ethnic and Geographic Inequities to Optimise New Zealand Stroke Care (REGIONS Care) Study. The findings showed that only 34.7% of ischemic stroke patients in urban hospitals and 32.5% of those in non-urban hospitals received a swallow assessment within 6 h of hospital arrival, with no significant difference between both groups (adjusted odds ratio 0.94, 95% confidence interval 0.74–1.18) [6]. Management of the other two FeSS Protocol elements (fever and hyperglycaemia) were not included in the audit hence it remains unclear whether or not these physiological parameters are being monitored and treated appropriately in New Zealand. The Australian and New Zealand audit results highlight that a significant evidence-practice gap remains in translation of the FeSS Protocols into standard stroke care across these countries. Achieving knowledge translation and sustaining adherence to evidence-based interventions is often difficult [7]. There is a need for systematic support to further improve adherence to the FeSS Protocols.

Successful implementation of research evidence into practice is influenced by the nature and type of evidence, the context in which the evidence is used, and use of an evidence-based implementation strategy [8, 9]. In particular, the need for appropriate facilitation as a strategy to improve the potential of implementation success has been emphasised [8]. Facilitation refers to the process of providing help and support to individuals and teams to enable them to achieve a specific goal by changing their behaviours [10]. Facilitation may occur in various forms, using either an external facilitator, an internal facilitator, or a combination of both [10]. Key roles of facilitators are to identify, engage and connect stakeholders; facilitate collaboration including the development of action plans; support communication and information sharing; and evaluate practice change [11]. Facilitator roles that have been examined in stroke include external facilitators providing ongoing remote or face-to-face support to clinicians to review hospital performance against clinical processes of care and develop an action plan [12, 13] and internal facilitators coordinating improvements in the organisation and delivery of stroke care [14, 15]. Evidence for the effectiveness of facilitation in the implementation of evidence into practice has also been demonstrated. Findings from a systematic review and meta-analysis showed a moderately robust effect for evidence-based guideline adoption following the use of practice facilitation [16]. A recent multicentre stepped-wedge cluster randomised trial demonstrated that externally facilitated educational outreach support aligned with routine collection of registry data, local consensus processes and tailored strategies has the potential to improve acute stroke care [17].

Our team have recently completed the QASC Europe project, a collaboration between the Nursing Research Institute, the European Stroke Organisation, the European Registry of Stroke Care Quality (RES-Q) and the European Acute Networks Striving for Excellence in Stroke (Angels) Initiative—a not-for-profit organisation that aims to optimise the quality of treatment in all stroke centres. This study provided further evidence for successful external remote facilitation resulting in international uptake of the FeSS Protocols into 67 European hospitals in 17 countries [18–20]. The results showed statistically significant improvement pre-to-post-implementation in overall FeSS Protocol adherence (Pre 3.4%, Post 35%; Absolute difference 33%, 95% CI 24%, 42%; *p*<0.0001 )[17]. In this pre-test/post-test study conducted amid the COVID pandemic, we used an external facilitation model whereby hospital clinical champions, supported by the Angels Initiative, implemented the FeSS Protocols with ongoing email and telephone support co-ordinated remotely from Australia. Consequently, the intervention was able to be successfully delivered simultaneously to multiple international stakeholders across Europe. The various stakeholder groups played different roles involving a flow of information and change management from one stakeholder level to another. We called this a Cascading Facilitation model which involved interlocking partnerships and supported facilitation [21].

There are many ways of providing facilitation which vary in their intensity, and level of resources required [10–15]. However, there is relatively little information about the effectiveness and cost-effectiveness of different facilitation models [13, 22, 23]. In particular, it is important to evaluate low-intensity/resource and high-intensity/resource approaches to identify effective and affordable facilitation models. Building on our previous research, this study will develop and test two different intensities of external remote (no face-to-face hospital visits by the research team) facilitation to support delivery of the FeSS Protocols for patients with stroke, at pace and on a large scale in two countries. Implementation of the FeSS Protocols will be informed by an integrated knowledge translation model [24]. This model incorporates evidence-based behaviour change implementation strategies (an online education package, audit and feedback reports, local clinical champions, barrier and enabler assessments, action plans, reminders and external remote facilitation) [25] and frameworks (Theoretical Domains Framework [TDF] [26], Capability, Opportunity, Motivation – Behaviour Model (COM-B system) [27] and the Consolidated Framework for Implementation Research [28]).

Cost-effectiveness studies evaluating the use of implementation strategies, including facilitation, in acute care settings are limited [29]. A study investigating changes in acute hospital costs before and after implementation of a stroke clinical facilitator programme found that the average cost per bed-day was higher post-implementation (AUD $878 per day) compared to pre-implementation (AUD $709). However, there was subsequent evidence of cost containment, with the average total inpatient costs per-episode decreasing by 10% over 4 years [30]. An independent economic evaluation estimated a gross economic benefit of AUD $281 million per year if the FeSS Protocols were implemented in 65% of the Australian stroke patient population [31]. A further study showed large societal and healthcare savings costs of AUD $251.7 million and AUD $65.2 million respectively for use of the FeSS Protocols over a 5-year period [32]. Consequently, we also will undertake a sub-study that includes an economic evaluation of the different facilitation strategies for implementing the FeSS Protocols.

A separate process evaluation will examine organisational, contextual and structural factors to successful uptake of the FeSS Protocols. Intervention fidelity will be examined as part of the main trial findings and reported as adherence with the FeSS Protocols as outlined in our outcome measures below.

### Study aims

The primary aim is to compare the effectiveness of high-intensity versus low-intensity external remote facilitation to support implementation of the FeSS Protocols to improve management of fever, hyperglycaemia and swallowing difficulties in the first 72 h of stroke unit/stroke service admission in Australia and New Zealand.

The secondary aims are to compare the effectiveness of (1) low-intensity facilitation with no facilitation, (2) high-intensity facilitation with no facilitation and (3) high- or low-intensity facilitation with no facilitation, to support implementation of the FeSS Protocols; (4) determine whether post-intervention changes in monitoring and treatment for fever, hyperglycaemia and swallowing differ between metropolitan and rural/remote hospitals; (5) determine whether post-intervention changes in monitoring and treatment for fever, hyperglycaemia and swallowing differ between stroke units and stroke services; (6) describe the potential cost-effectiveness of the different facilitation methods (economic evaluation); and (7) identify clinicians’ views regarding factors that influence uptake of the FeSS Protocols in metropolitan and rural/remote hospitals (process evaluation).

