## Methods

### Study design

A three-arm cluster randomised controlled trial with a theory-based process evaluation will be undertaken. Hospitals (clusters) will be randomised to the multicomponent implementation strategy delivered with high or low external remote facilitation or a no facilitation control group receiving only usual care (inactive control group).

This protocol complies with the Standard Protocol Items: Recommendations for Interventional Trials (SPIRIT) [33], CONSORT extension for cluster randomised trials [34] and Template for Intervention Description and Replication (TIDiER) [35] checklists (Additional files 1, 2 and 3).

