### Control group

Hospitals randomised to the control group will only have access to the publicly available FeSS Protocols. No active intervention/external remote facilitation will be provided by the researchers, and these hospitals will perform usual stroke care practices and collect data on the FeSS processes of care. Control group hospitals will not receive the detailed FeSS audit and feedback reports that will be provided to intervention group hospitals. However, there may be some hospitals randomised to the control group that participate in the biennial national stroke acute care audits and/or contribute continuous data on the FeSS elements to the AuSCR. As per standard practice, these hospitals will routinely receive basic audit and feedback reports from the Stroke Foundation and/or AuSCR as part of quality improvement initiatives undertaken external to the trial. If the research team receive any proactive emails from control group hospitals regarding the study (excluding questions about data collection), these hospitals will be directed to the Quality in Acute Stroke Care webpage hosted on the Australian Catholic University website (https://www.acu.edu.au/qasc). If the questions relate to the national stroke audit or AuSCR data entry or platform issues, they will be referred to the national stroke audit coordinator or AuSCR, as required. At study completion, clinical champions from control group hospitals will receive access to the online FeSS education package after providing their post-implementation data.

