### Economic evaluation

An economic evaluation will include a cost-consequence analysis to evaluate the costs and benefits of the external remote facilitation (low and high) interventions, relative to control. We will also assess the potential cost-effectiveness of the interventions compared with control by estimating incremental cost-effectiveness ratios (ICERs) [63]. All costs will be presented based on the 1-year period of the QASC Australasia programme. Cost will be converted into Australian/New Zealand dollars using a nominal rate method and adjusted for inflation where necessary. The additional costs of implementing the FeSS Protocols will be informed by financial records kept by the researchers. Other additional costs or cost savings due to the implementation of the FeSS Protocols will be considered based on the findings of the clinical evaluation, the findings of the process evaluation, and consultation with the researchers.

Data on health benefits will be derived in a sub-study of this cluster randomised controlled trial. This sub-study will only include trial hospitals that contribute data to the AuSCR [64] or the New Zealand Stroke Registry because the registries collect 90–180-day patient outcome data required for the economic evaluation. For this subset of hospitals contributing FeSS data to the registry [64], patient hospital data collected in the Australian Stroke Data Tool together with the follow-up survey data collected between 90 and 180 days from the AuSCR will be used. Quality-adjusted life years (QALYs) will be estimated by applying utility scores according to the modified Rankin Scale at discharge from hospital, from data obtained at a follow-up assessment conducted at 90–180 days post-stroke as part of the AuSCR and survival status determined through routine linkage of the AuSCR with the National Death Index. Responses to the EQ-5D-3L questionnaire at 90–180 days post-stroke will be converted into a utility score using an algorithm developed in an Australian population [65].

Data from the study will be supplemented in the economic analysis models by applying estimates from the published literature on treatment effect, discharge destination and outcomes, as required. The economic evaluation will be reported according to the Consolidated Health Economic Evaluation Reporting Standards [66], and the findings may be used to model the potential benefits of FeSS implementation state-wide or Australia-wide.

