## Discussion

In healthcare settings, facilitation aims to support a sustainable evidence-informed practice change based on an identified gap in clinical performance, with the goal of improving patient outcomes [72]. It ranges from providing task-oriented assistance to enabling individual clinicians and hospital units to alter their ways of thinking and working [73]. Our prior work in Europe has shown that an external remote facilitation approach can be successfully used for large-scale translation of the FeSS Protocols. Despite this evidence, the optimal intensity needed to effectively implement the Protocols into clinical practice remains unknown. This three-arm cluster randomised controlled trial will use a theory-informed behaviour change multicomponent implementation strategy to test the type of external remote facilitation needed to improve implementation of the FeSS Protocols for stroke patients in Australia and New Zealand. Stroke unit/stroke service clinicians will be supported to implement the FeSS Protocols in the context of a recognised need for improvement in stroke care practice.

For our pragmatic implementation trial [74], we have chosen the multi-arm (three-arm) parallel-group randomised trial design. Multi-arm randomised trials in general have the advantage of comparing multiple implementation strategies compared to two-arm trials [75, 76]. This is a key strength of our study as this design provides the opportunity to compare different doses of facilitation thereby increasing the possibility of detecting an effective dose.

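### Secondary aims 1–3 call the comparisons with control facilitation versus no facilitation, but control also lacks the rest of the implementation strategy

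*Protocol article*

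**What the plan says.** Study aims sets the primary aim as high- versus low-intensity external remote facilitation. The first three secondary aims are "1) low-intensity facilitation with no facilitation, (2) high-intensity facilitation with no facilitation and (3) high- or low-intensity facilitation with no facilitation". The contributions statement (under Supplementary Information) says that the study "will test whether high- or low-intensity external remote facilitation versus no external facilitation is more effective". The Discussion says that the three-arm design "provides the opportunity to compare different doses of facilitation thereby increasing the possibility of detecting an effective dose". The Economic evaluation section will "evaluate the costs and benefits of the external remote facilitation (low and high) interventions, relative to control".

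Study design describes the arms differently. There the active arms get a strategy made of several components, and the allocation is worded as "delivered with high or low external remote facilitation or a no facilitation control group receiving only usual care (inactive control group". The Control group section adds: "Hospitals randomised to the control group will only have access to the publicly available FeSS Protocols"; "Control group hospitals will not receive the detailed FeSS audit and feedback reports that will be provided to intervention group hospitals"; and, at study completion, "clinical champions from control group hospitals will receive access to the online FeSS education package after providing their post-implementation data".

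**The concern.** The aims and the contributions statement name the contrasts with control as if facilitation were the only thing that differs. Study design and Table 1 show that a whole package differs. A reader who takes the aims at their word would read a positive low-versus-control or high-versus-control result as evidence that facilitation works, although education, feedback and action planning could have produced some or much of it.

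This matters for use of the results. The Discussion plans a business case built on the most effective facilitation intervention. A health service deciding whether to pay for facilitators, or only for an online course and a feedback report, needs to know which of these the contrast with control speaks to. It speaks to the package as a whole.

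**Working it through.** No sample size, power or error-rate figure bears on this point. The check compares components by arm and then asks what each contrast identifies.

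**Components by arm** (Table 1; Table 3; Local team meeting to assess barriers and develop action plan; Table 5; Table 6; Control group; Table 7)

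| Component | High | Low | Control |
|---|---|---|---|
| FeSS Protocols | yes | yes | yes |
| Online education package | yes | yes | no, some hard-copy files only |
| Detailed audit and feedback report | yes | yes | no |
| Barrier meeting with action plan | yes | yes | no |
| Intervention reminders | yes | yes | no |
| Reactive email and telephone support | yes | yes | no |
| Videoconferences and facilitator guidance | yes | no | no |
| Proactive email and telephone contact | yes | no | no |
| Process and data-collection reminders | yes | yes | yes |

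Table 3 gives control the protocols, the ASSIST slides, the data dictionary, the data collection manual and the FAQ. It does not give control the videos, the meeting slides or the action plan template. Clinical champions are not counted as a difference, because every hospital must have one to be eligible.

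**What counts as facilitation.** The Background and the Implementation strategy section list education, audit and feedback, barrier assessments, action plans and reminders beside external remote facilitation, as separate components. Table 1 agrees, except that it files reminders under facilitation.

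**Count of differences**
- Low versus control: 5 components. Under Table 1, 2 are facilitation (intervention reminders, reactive support) and 5 − 2 = 3 are not. Under the Implementation strategy list, reminders are separate, so 1 is facilitation and 5 − 1 = 4 are not.
- High versus control: 5 + 2 = 7 components, with the same 3 (or 4) that are not facilitation.
- High versus low: 2 components, both facilitation.

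**What each contrast identifies.** On the log-odds scale, let b be the effect of the package without facilitation against usual care. Let f_L and f_H be the further effects of adding low or high facilitation to that package. Then:
- Low − control = b + f_L (aim 1)
- High − control = b + f_H (aim 2)
- Either − control = b + an average of f_L and f_H, about b + (f_L + f_H)/2 with equal active arms (aim 3)
- High − low = (b + f_H) − (b + f_L) = f_H − f_L (primary aim)

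Three arms give two independent contrasts for three unknowns. Only b + f_L, b + f_H and their difference can be estimated. To isolate f_L or f_H would need an arm with the package and no facilitation, and there is none. In the primary contrast b cancels.

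**Where it is sharpest.** In the low arm, f_L comes from little. The External remote facilitation section says that low-intensity champions get no guidance from the facilitators. Table 1 gives them no videoconferences, and Table 6 limits their email and telephone support to reactive contact. Low versus control is thus mainly a comparison of the package with usual care.

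**The case against.** The strongest reply is that the composition of the arms is disclosed. Study design states the contrast correctly, the abstract places facilitation within a multifaceted intervention, and Table 1 and the Control group section itemise what control lacks. On that view, no facilitation is just an arm label. The Data analysis section already compares with control groups and plans pairwise comparisons only. All of this stands, and it shows that the fault is mislabelling, not concealment. It does not rescue the aims, which state the question as facilitation against none and so disagree with Study design.

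A second reply is that the boundary is blurred. The Background counts helping to develop action plans among facilitator roles, facilitators grant access to the education package, and the action plan template sits inside that package. This makes the exact count arguable. It does not remove the online education or the feedback report from the list of things that control lacks, and the protocol's own lists name each of them separately from facilitation.

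Some stronger readings are tempting, and the documents do not support them:
- **That the cost-effectiveness ratios set the cost of facilitation alone against the benefit of the whole package.** The Economic evaluation section, Table 7 and Outcome measures refer to the costs and gains of implementing the FeSS Protocols, and nothing restricts the costs to facilitation. Only the label is at fault.
- **That the whole low-versus-control effect would be misattributed if reactive support did nothing.** Table 1 also places intervention reminders under facilitation, and no size for either effect is given.
- **That a none–low–high dose trend is planned.** It is not. The Discussion's remark on doses fits high versus low, and goes wrong only if control is read as the zero dose.
- **That control receives nothing from the education package.** Table 3 gives it some hard-copy files.

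**Conclusion.** The point holds for secondary aims 1–3 and the contributions statement. Three non-facilitation components (four if reminders count separately) are completely aliased with any facilitation, so a facilitation-versus-none effect cannot be identified from these arms. A statistical analysis plan could not recover it.

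The comparisons with control remain valid randomised estimates of the multicomponent strategy, including facilitation, against usual care. The primary comparison is unaffected, because both active arms share the package. How much of any difference from control is due to facilitation cannot be known from this design, and no share is assumed here. The conclusion rests on the arms being delivered as Table 1 and the Control group section describe. It is worth correcting because it changes what may be concluded, but it does not undermine the trial.

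**What to change.** - In Study aims, restate secondary aims 1–3 as the multicomponent implementation strategy with low-intensity, high-intensity or either-intensity facilitation versus usual care.
- Restate the contributions statement in the same terms.
- In the Economic evaluation section, label the interventions compared with control the same way.
- State that only the randomised high-versus-low comparison supports a conclusion about facilitation intensity. Qualify the Discussion sentence on doses so that control is not treated as the zero dose.

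This changes wording only. Arms, data, models and sample size stay as they are. The cost is a narrower claim: the comparisons with control can show that the strategy as a whole works, but not that facilitation does.
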